# Evaluating telehealth lifestyle therapy versus telehealth psychotherapy for reducing depression in adults with COVID-19 related distress: the curbing anxiety and depression using lifestyle medicine (CALM) randomised non-inferiority trial protocol

**DOI:** 10.1186/s12888-022-03840-3

**Published:** 2022-03-27

**Keywords:** Diet, Nutrition, Exercise, Physical activity, Depression, Mental health, Psychotherapy, Psychiatry, Mental disorders

## Abstract

**Background:**

There is increasing recognition of the substantial burden of mental health disorders at an individual and population level, including consequent demand on mental health services. Lifestyle-based mental healthcare offers an additional approach to existing services with potential to help alleviate system burden. Despite the latest Royal Australian New Zealand College of Psychiatrists guidelines recommending that lifestyle is a ‘first-line’, ‘non-negotiable’ treatment for mood disorders, few such programs exist within clinical practice. Additionally, there are limited data to determine whether lifestyle approaches are equivalent to established treatments. Using an individually randomised group treatment design, we aim to address this gap by evaluating an integrated lifestyle program (CALM) compared to an established therapy (psychotherapy), both delivered via telehealth. It is hypothesised that the CALM program will not be inferior to psychotherapy with respect to depressive symptoms at 8 weeks.

**Methods:**

The study is being conducted in partnership with Barwon Health’s Mental Health, Drugs & Alcohol Service (Geelong, Victoria), from which 184 participants from its service and surrounding regions are being recruited. Eligible participants with elevated psychological distress are being randomised to CALM or psychotherapy. Each takes a trans-diagnostic approach, and comprises four weekly (weeks 1-4) and two fortnightly (weeks 6 and 8) 90-min, group-based sessions delivered via Zoom (digital video conferencing platform). CALM focuses on enhancing knowledge, behavioural skills and support for improving dietary and physical activity behaviours, delivered by an Accredited Exercise Physiologist and Accredited Practising Dietitian. Psychotherapy uses cognitive behavioural therapy (CBT) delivered by a Psychologist or Clinical Psychologist, and Provisional Psychologist. Data collection occurs at baseline and 8 weeks. The primary outcome is depressive symptoms (assessed via the Patient Health Questionnaire-9) at 8 weeks. Societal and healthcare costs will be estimated to determine the cost-effectiveness of the CALM program. A process evaluation will determine its reach, adoption, implementation and maintenance.

**Discussion:**

If the CALM program is non-inferior to psychotherapy, this study will provide the first evidence to support lifestyle-based mental healthcare as an additional care model to support individuals experiencing psychological distress.

**Trial registration:**

Australia and New Zealand Clinical Trials Register (ANZCTR): ACTRN12621000387820, Registered 8 April 2021.

## Background

The burden of common mental disorders continues to grow with substantial impacts on health and major social and economic consquences globally [1]. While psychological interventions have been an effective treatment for mild-to-moderate depression and have shown comparable outcomes to pharmacotherapy [2], the increased demand for mental healthcare has caused lengthy waitlists for individuals seeking care for psychological distress [3]. For individuals in rural or remote communities, access to care is even more limited. Moreover, a proportion of individuals do not achieve full remission of symptoms from psychotherapy [4] or have a desire to seek other treatment options [5]. There is an urgent need for alternative approaches to established therapy which may alleviate the burden on mental health services, including responsive and flexible delivery models that reach those experiencing barriers to accessing conventional care.

Efficacy data supporting the use of lifestyle therapies as an adjunctive treatment for mental disorders are consistent and increasingly compelling [6]. A 12-week whole-of-diet intervention in 67 participants with moderate-to-severe depression was efficacious for reducing clinical depression [7]. It also found a cost saving of approximately $2600 per participant in the dietary condition due to reduced healthcare costs and reduced absenteeism [8]. A group-based study taking a similar approach to depression treatment yielded comparable findings and was also shown to be highly cost-effective [9]. These studies—backed up by level 1 evidence for dietary support to reduce depressive symptoms for a range of health conditions [10]—point to the potential of lifestyle therapies for producing large health benefits and cost savings in people with mental illness. Meta-analyses show physical activity interventions are also efficacious in treating depression [11, 12]. Literature reviews and preliminary experimental work indicate that physical activity can provide positive effects on neural structures [13], mental health [12, 14] and cognitive function [15]. These benefits also appear in the absence of clinical disorders, with a recent study reporting that an 8-week resistance exercise program significantly reduced anxiety symptoms in young adults without generalised anxiety disorder [16].

Telephone or web-based delivery is accepted increasingly as a feasible and effective delivery method for lifestyle programs [17]. ‘Telehealth’ refers to healthcare delivered via communications technologies rather than ‘in person’. Additionally, in the context of restricted physical mobility and pre-existing mental health concerns (such as agoraphobia and social anxiety), telehealth programs are highly applicable. A multimodal, integrated lifestyle telehealth intervention showed considerable promise for reducing depressive symptoms (assessed using the Patient Health Questionnaire 9 (PHQ-9)) compared to standard care, especially for those with a history of depression after a heart attack [18]. In addition, home exercise prescribed using a web-based exercise program resulted in higher confidence and engagement in physical activity compared to standard care [19]. As of 2021, the Australian Government identified telehealth delivery of mental health interventions as a key model of care [20].

The COVID-19 pandemic has led to further deteriorations in mental health and applied strain to mental health services. Compared to before the pandemic, the COVID-19 Mental Disorders Collaborators estimate that globally there has been a 27.6% increase in major depressive disorder cases and a 25.6% increase in anxiety disorders [21]. In addition to the direct impact of the disease itself (i.e. infection, fear of infection, loss of loved ones), the indirect impact of public health policy to promote infection control (such as lockdowns and restricted freedoms) may have exacerbated mental health symptoms in those with pre-existing mental health concerns [22]. Physical isolation may induce boredom, loneliness, frustration, anger, post-traumatic stress, financial loss, and stigma [23]—even in those with no history of mental illness. The deleterious effects of loneliness on health is equivalent to that of smoking [24]. It has been shown that, people living in the Australian state of Victoria, who have undergone the longest period of ‘lockdown’ anywhere in the world, have increased odds of experiencing clinically significant symptoms of depression and anxiety compared to those living in other areas of the country with less extensive lockdowns and restrictions [25]. This cohort also had significantly decreased odds of having high optimism about the future [25].

Despite the Royal Australian New Zealand College of Psychiatrists guidelines explicitly recommending that lifestyle approaches be a ‘first-line’, ‘non-negotiable’ treatment for mood disorders [26], there are surprisingly few studies from real world settings to guide implementation, nor to demonstrate their effects relative to an established psychotherapy. This paper presents the study protocol for the CALM (Curbing Anxiety and depression using Lifestyle Medicine) randomised controlled trial based in Victoria, Australia. The aim is to examine the relative effectiveness and cost-effectiveness of an integrated lifestyle program (CALM) compared to an established psychotherapy program—both delivered via telehealth. We hypothesise that the CALM program will not be inferior to the psychotherapy program for depressive symptoms (PHQ-9 scores) at 8 weeks.

## Methods

### Study design

This is a two-arm, parallel-group, individually randomised group treatment (IRGT), non-inferiority trial. This single-site study is currently recruiting *N* = 184 participants from the Barwon and surrounding regions (Victoria, Australia). Participants are individually randomised (1:1 allocation) to either of the two group-based programs, both delivered via telehealth. All participants complete assessments prior to randomisation (baseline) and at program completion (8 weeks). Recruitment and program delivery are anticipated to occur over 50 weeks, from May 2021 to April 2022.

### Study aims

The primary aim is to examine the effectiveness of the CALM program for reducing depressive symptoms compared to a standard psychotherapy program. The primary outcome will be change in depressive symptoms at 8 weeks as measured by the Patient Health Questionnaire-9 (PHQ-9) [27]. Secondary aims include: (i) examination of the efficacy of CALM versus psychotherapy on other health outcomes (anxiety symptoms, psychological distress, health behaviours, health functioning and cardiovascular disease biomarkers), (ii) investigation of the cost-effectiveness of the CALM program relative to psychotherapy from healthcare and societal perspectives, and (iii) a process evaluation by which to determine the reach, adoption, implementation and maintenance (RE-AIM) [28] of the CALM program beyond the research period.

### Participant eligibility

Participants are included if they are adults (aged 18 years or older), have capacity to provide informed consent, can converse in English, are willing to commit to six 90-min sessions over an 8-week period, have basic computer and internet literacy (able to access Zoom calls), and have a Distress Questionnaire-5 (DQ5) [29] score > 8 at enrolment. Participants are excluded if they have a known or suspected clinically unstable systemic medical disorder; severe food allergy, intolerance, aversions or malabsorption issue; a current or lapse/relapse of an eating disorder; or any other socio-cultural, religious, medical reasons which precludes their participation in a lifestyle intervention. During this trial period, participants cannot be involved in another intervention study. Participants cannot be pregnant, breastfeeding, or planning pregnancy within the next year. Participants are asked to provide blood and stool samples on two occasions (pre- and post-intervention). As this study aims to determine the effectiveness of the CALM intervention as an adjunctive therapy, ongoing pharmacological or other treatments during the intervention period is not an exclusion criterion. However, participants are excluded if they commence a new, duplicating treatment (e.g., psychotherapy) for a mental illness within a 1-month period prior to baseline or are experiencing an exacerbation of symptoms not adequately controlled by medication. Finally, participants must be deemed suitable for participation in a structured lifestyle or psychotherapy program for 8 weeks (i.e. not in crisis or suicidal at time of enrolment). Where evidence of acute suicidality or mental health crisis is identified during enrolment, a risk screening is conducted by a mental health clinician (TJ) to determine eligibility for participation. Individuals identified as in crisis or suicidal are directed to specialty services. Participants without access to a device and/or stable internet are loaned a device with mobile data.

### Recruitment and informed consent

The primary recruitment strategy is through Continuing Care Services (CCS) within the Barwon Health Mental Health, Drugs & Alcohol Service (MHDAS) in Geelong, Victoria, Australia. CCS provide medium-to-long term mental health services in community settings for consumers of all ages across the regional setting of Geelong and the surrounding regions (South West Victoria). Based on Australian remoteness classifications, this region covers Metropolitan Areas, Regional Centers, Large Rural Towns, Medium Rural Towns, and Small Rural Towns. A Referral Coordinator employed and based at MHDAS identifies potentially eligible participants from patient databases and case files and sends them an invitation to participate. This letter contains information about the study requirements and invites them to contact a member of the Deakin research team if they are interested in participating. To avoid potential coercion, the research team does not contact potential participants from MHDAS unless they have expressed interest.

Recruitment also occurs through community-based advertising such as flyers displayed around Deakin University campuses, Barwon Health sites, community hubs and General Practice clinics, media releases, newspaper articles, radio interviews, community talks and social media. Mental health services (e.g. Headspace) supports recruitment by providing flyers to clients at entry point and/or at assessment, with the objective of informing them of the trial and encouraging them to consider participating whilst on waiting list for headspace services and/or as an adjunct to headspace services.

Interested individuals undergo a brief eligibility check (including the DQ5, [29]) conducted over the phone with a study coordinator. If at any time they are identified as not meeting the inclusion criteria, they are informed that they are not eligible for inclusion in the trial but are provided with information on where to seek support. Eligible participants are invited to enrol in the study. Once e-consent is obtained, baseline assessments are booked at a time convenient to the participant.

Due to the individually randomised group treatment design, baseline assessment of eligible participants are ‘batched’ to ensure 50/50 randomisation to each arm whilst reducing the amount of time between baseline assessments and commencement of the program to which they have been assigned. In other words, baseline assessments are booked only once an adequate number of participants have enrolled to form groups (minimum 5, maximum 10, per group). At this point, participants are asked whether they have had any changes to medications or medical events since enrolment. If the time from enrolment to time of baseline assessments exceeds 2 weeks, they are re-assessed on the DQ5 to re-confirm eligibility.

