### Data collection

To minimise interruptions caused by COVID-19 lockdowns, data collection is designed to involve minimal face-to-face contact. Demographic data (including age, sex, ethnicity, postcode, medications, nominated General Practitioner or case manager) are obtained via phone interview upon enrolment. At both baseline and 8-week follow-up, the blinded research assistant administers a battery of questionnaires via a Computer-Assisted Telephone Interview (CATI). This CATI takes approximately 30-60 min to complete and is conducted by a research assistant with specialised training. In addition to the CATI, the Mini-International Neuropsychiatric Interview (MINI) is administered in a separate Zoom call by a trained Clinical Psychologist or Provisional Psychologist. The MINI is a structured diagnostic interview designed to assess 17 of the most common mental health disorders [30]. It is used here to examine the prevalence of current and past major psychiatric disorders in the trial population.

In the absence of any COVID-19 related lockdown, consenting participants are also invited to complete an in-person visit at Australian Clinical Labs Collection Centre and Health Education and Research Building (both in Geelong). This visit cannot be administered via telephone. It includes a fasting blood test; weight, height, waist and hip measurements; blood pressure assessments; and muscular strength tests. Stool samples are provided by participants and returned via the post and stored in laboratory facilities at the Research Centre. As research assistants conducting data collection are blinded to participants’ program allocation, prior to the 8-week follow-up assessments participants are reminded not to reveal the group they have been assigned to in order for research assistants to retain blinded status.

If a participant chooses to withdraw from the study or is withdrawn by the research team (due to an adverse event, violating inclusion criteria, or if continuing would be detrimental to their wellbeing), data collected up until that time point will be used in the analysis of results, unless otherwise requested by the participant. A research assistant will also make a reasonable attempt to collect the primary outcome from withdrawing participants by organising a follow-up CATI.

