#### Randomization and blinding

Upon enrolment, participants are assigned a unique study identification (ID) number for randomisation purposes. After baseline assessment is complete, participants are assigned randomly to either the CALM group or the psychotherapy group. Allocation to the intervention arm is conducted using computer-generated block randomisation in a 1:1 ratio (CALM to psychotherapy). The allocation sequence is generated by an independent statistician. As randomisation occurs only when there are sufficient participants to form groups (minimum *n* = 5 per group), block randomisation is not feasible. Rather, a simple random allocation method is used within groups of participants which are ready to be randomised.

The Study Coordinator (unblinded) provides each participant with the schedule (for the group to which they have been allocated) and the technical support information (e.g., Zoom download, set up).

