### Data analyses

To compare continuous outcomes on the PHQ-9 in the primary analysis, between-group mean difference and confidence intervals (CIs) will be estimated using generalised estimating equation techniques, with Huber Sandwich Estimator of variance to account for clustering [31, 73]. One-sided type I error of 0.025 will be used for all non-inferiority analyses. Effect sizes will be calculated using Cohen’s d. Exploratory analyses non-equivalence comparisons will examine remission (post-treatment score < optimal cut-score for a probable diagnosis of depression on PHQ-9 in participants who initially scored above Threshold) and recovery rate (reduction of at least 50% of pre-treatment PHQ-9 scores) rates. Two-sided alpha of 5% will be used. Reliable improvement is defined as a reduction of > 5 points on PHQ-9 scores based on severity classifications pre-to-post treatment.

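### Participants are randomised within calendar batches, but the primary GEE states no batch term and names no cluster unit; if it clusters by therapy group, the standard error is overstated and power is lost

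*Protocol article*

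**What the plan says.** Under Recruitment and informed consent, the protocol article explains that enrolment is batched: "baseline assessments are booked only once an adequate number of participants have enrolled to form groups", with group size given as "minimum 5, maximum 10, per group". One stated purpose of batching is "to ensure 50/50 randomisation to each arm". Randomization and blinding confirms that the waiting set is the unit within which allocation happens: "Rather, a simple random allocation method is used within groups of participants which are ready to be randomised".

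Study design gives the calendar span: "Recruitment and program delivery are anticipated to occur over 50 weeks, from May 2021 to April 2022". Data collection shows that lockdowns were expected in that period: "To minimise interruptions caused by COVID-19 lockdowns, data collection is designed to involve minimal face-to-face contact".

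Data analyses fixes the primary method as a GEE estimate of the mean PHQ-9 difference "with Huber Sandwich Estimator of variance to account for clustering". That section does not say what the cluster is and lists no covariates. Sample size gives a margin of 2 points, SD 4, a one-sided error of 0.025 (a one-sided 5% is also mentioned) and 80% power. It gives no figure for variation between batches or between therapy groups.

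**The concern.** The batch is in effect the randomisation stratum. Batches are spread over most of a year, and both arms are drawn from each one. Whatever raises or lowers PHQ-9 in a whole batch (season, restrictions, source of referral) affects both arms of that batch and largely drops out of the difference between them.

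A sandwich variance taken by therapy group treats the CALM group and the psychotherapy group of one batch as independent. The variation between batches then enters the estimated variance of the arm comparison, although the comparison does not carry it. A balance that the design creates is given away in the analysis. At stake is precision: the conclusion depends on a confidence limit staying below 2 points, and an interval wider than it needs to be makes that harder to reach.

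**Working it through.** **Inputs from the article.** Margin 2, SD 4, one-sided 0.025, N = 184 randomised, groups of 5 to 10.

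**Assumptions, not in the article.** One group per arm per batch; mean group size 7.5 (middle of 5 to 10); 85% evaluable, so m = 7.5 × 0.85 = 6.375; therapy-group ICC rg = 0.03; batch ICC rb from 0 to 0.10. With 184/2 = 92 per arm, 92/7.5 ≈ 12 batches (92/10 ≈ 9 to 92/5 ≈ 18).

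**The plan's own figure.** No batch figure exists to reproduce. The sample size inputs give 2 × 4² × (1.96 + 0.8416)² / 2² = 62.8, so 63 per arm, not the stated 80. That mismatch is a separate matter. Here it shows only that the stated inputs contain no allowance for batch.

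**Variance of a group mean, as a share of total variance**
- As counted by a group-level sandwich: rb + rg + (1 − rb − rg)/m
- As it bears on the within-batch difference: rg + (1 − rb − rg)/m
- Ratio of estimated to true standard error (SE): the square root of the first over the second

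| rb | (1 − rb − rg)/m | counted | bearing on difference | SE ratio |
|---|---|---|---|---|
| 0 | 0.1522 | 0.1822 | 0.1822 | 1.000 |
| 0.02 | 0.1490 | 0.1990 | 0.1790 | 1.054 |
| 0.05 | 0.1443 | 0.2243 | 0.1743 | 1.134 |
| 0.10 | 0.1365 | 0.2665 | 0.1665 | 1.265 |

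On the PHQ-9 scale with 12 batches, SE = 4 × √(2 × share / 12). At rb = 0.05 this is 0.773 estimated against 0.682 true; at 0.10, 0.843 against 0.666.

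**Simulation, 12 batches, rg = 0.03, true difference 0 for power.** Clustering by therapy group with no batch term gave a mean SE of 0.76 against a true 0.67 at rb = 0.05, and 0.83 against 0.67 at 0.10. One-sided type I error was about 0.01, and power was 72% and 65%. A balanced-data version of a model with random intercepts for batch and for group within batch kept type I error at 0.015 to 0.029. Its power was about 79% at both values, and 79% against 78% at rb = 0.

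**Second simulation, 160 analysed, rg = 0.05, batch share 10%, batch as a fixed effect for comparison**
- 16 batches of 10: no batch term, SE about 0.80 against a true 0.68 to 0.70, type I error 0.012 to 0.013, power 0.69 to 0.70. With the term, type I error 0.023 to 0.026, power 0.77 to 0.79.
- 8 batches of 20: no batch term, type I error about 0.007, power 0.48 to 0.49. With the term, about 0.025 and 0.64.
- Batch share 0: the fixed term costs power, from 0.79–0.80 to 0.73–0.77 with 16 batches and from 0.68 to about 0.60–0.62 with 8.
- With rg = 0, taking the sandwich by batch and adding no batch term also kept type I error close to nominal (0.023 to 0.030).

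**The case against.** The strongest reply is that this article is silent rather than wrong. It names neither the cluster unit nor any covariate, and a condensed article commonly leaves both to the analysis plan. If the sandwich is taken by batch, the overstatement does not arise. This stands in part: one cannot say that the trial has decided to ignore batch. But the article does fix the estimator and the variance method, and the ordinary reading of clustering in this design is the therapy group. On that reading the stated analysis does not match the stated randomisation.

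A reader might infer that differences between batches bias the comparison or raise the chance of a false non-inferiority finding. The documents do not support that. With both arms in each batch the estimate is unbiased, and the simulated type I error falls below 0.025.

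A reader might also take the Background as showing that lockdowns shift PHQ-9 from batch to batch. It compares Victoria with areas under lighter restrictions, not successive batches in one region. It makes such shifts plausible but gives no size.

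Three further points stand. One group per arm running concurrently in each batch is inferred. Simple allocation does not guarantee the equal group sizes used in the formula. Study aims describes the primary outcome as change at 8 weeks; if the analysis uses change or adjusts for baseline, lasting batch differences are partly removed and the relevant batch ICC is smaller.

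The objection that a batch adjustment costs power when batches do not differ holds for the fixed-effect and batch-level versions. In the balanced simulation it did not hold for the random-intercept model.

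**Conclusion.** The point holds as a loss of precision. If the sandwich is taken by therapy group, without a batch term, and each batch feeds both arms, the estimated SE is too large whenever batches differ. Under the stated assumptions the overstatement is 0%, 5%, 13% and 26% at batch ICCs of 0, 0.02, 0.05 and 0.10. With 12 batches, respecting the batch would raise power from 72% to about 79% at batch ICC 0.05, and from 65% to about 79% at 0.10.

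These sizes rest on an assumed batch variance, therapy-group ICC, group size and number of batches, none of which the article gives. They shrink if baseline absorbs part of the batch differences and vanish if batches do not differ. The validity of a positive non-inferiority finding is not threatened; the risk is failing to show non-inferiority when it is true. The change is worth making because it follows the randomisation and costs almost nothing.

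**What to change.** Before unblinding, state the cluster unit and make the primary analysis respect the randomisation batch, in one of two ways:

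- Fit random intercepts for batch and for therapy group within batch, with Kenward-Roger degrees of freedom. This is preferred, as it showed no material power loss at a batch ICC of 0.
- Keep the GEE and take a small-sample-corrected sandwich at batch level. If batch is also fitted as a fixed effect, the sandwich must still be at batch level, because clustering by therapy group with batch fixed effects understates the variance.

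State also whether each batch always forms groups in both arms over the same weeks, and whether baseline PHQ-9 enters the model.

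The cost is wording in the analysis plan. Batch is known for every participant from the randomisation process, so no new data are needed. The downside is negligible for the random-intercept model. For the batch-level or fixed-effect version it is some lost denominator degrees of freedom, and hence some power, if batches turn out not to differ.
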